# The effectiveness of a computer-aided system in improving the detection rate of gastric neoplasm and early gastric cancer: study protocol for a multi-centre, randomized controlled trial

**DOI:** 10.1186/s13063-023-07346-5

**Published:** 2023-05-11

**Keywords:** Artificial intelligence, Early gastric cancer, Randomised controlled trial

## Abstract

**Background:**

This protocol is for a multi-centre randomised controlled trial to determine whether the computer-aided system ENDOANGEL-GC improves the detection rates of gastric neoplasms and early gastric cancer (EGC) in routine oesophagogastroduodenoscopy (EGD).

**Methods:**

*Study design*: Prospective, single-blind, parallel-group, multi-centre randomised controlled trial.

*Settings*: The computer-aided system ENDOANGEL-GC was used to monitor blind spots, detect gastric abnormalities, and identify gastric neoplasms during EGD.

*Participants*: Adults who underwent screening, diagnosis, or surveillance EGD.

Randomisation groups:

1. Experiment group, EGD examinations with the assistance of the ENDOANGEL-GC;

2. Control group, EGD examinations without the assistance of the ENDOANGEL-GC.

*Randomisation*: Block randomisation, stratified by centre.

*Primary outcomes*: Detection rates of gastric neoplasms and EGC.

*Secondary outcomes*: Detection rate of premalignant gastric lesions, biopsy rate, observation time, and number of blind spots on EGD.

*Blinding*: Outcomes are undertaken by blinded assessors.

*Sample size*: Based on the previously published findings and our pilot study, the detection rate of gastric neoplasms in the control group is estimated to be 2.5%, and that of the experimental group is expected to be 4.0%. With a two-sided α level of 0.05 and power of 80%, allowing for a 10% drop-out rate, the sample size is calculated as 4858. The detection rate of EGC in the control group is estimated to be 20%, and that of the experiment group is expected to be 35%. With a two-sided *α* level of 0.05 and power of 80%, a total of 270 cases of gastric cancer are needed. Assuming the proportion of gastric cancer to be 1% in patients undergoing EGD and allowing for a 10% dropout rate, the sample size is calculated as 30,000. Considering the larger sample size calculated from the two primary endpoints, the required sample size is determined to be 30,000.

**Discussion:**

The results of this trial will help determine the effectiveness of the ENDOANGEL-GC in clinical settings.

**Trial registration:**

ChiCTR (Chinese Clinical Trial Registry), ChiCTR2100054449, registered 17 December 2021.

**Supplementary Information:**

The online version contains supplementary material available at 10.1186/s13063-023-07346-5.

## Introduction

Gastric cancer is the fourth leading cause of cancer-related deaths, with an estimated 1,080,000 new cases and 760,000 deaths in 2020 [1]. Early gastric cancer (EGC) is generally asymptomatic; therefore, most patients are not diagnosed until the disease has progressed to an advanced stage, with a 5-year survival rate of < 25% [2]. Early detection is vital to improve the prognosis of patients with gastric cancer [3].

Upper gastrointestinal endoscopy is widely used to detect and diagnose early gastric cancers [4]. White light endoscopy (WLE) is the current standard and most commonly used tool [5]. However, the diagnostic performance of WLE is not satisfactory, with a pooled sensitivity of 48.0% (95% confidence interval [CI], 39.0–57.0%) and a pooled specificity of 67.0% (95% CI, 62.0–71.0%) [6]. To improve diagnostic ability, new techniques such as image-enhanced and magnifying endoscopy have been proposed [7, 8]. However, the high cost of equipment, complex diagnostic theories, and strict training requirements for endoscopists limit the popularity of these techniques. Thus, the findings of this study are of great importance and have the potential to improve the diagnostic ability of WLE.

Despite its diagnostic ability, the quality of endoscopic examination plays an important role in the detection of EGC, which is a prerequisite for lesion detection [9]. To ensure endoscopic quality, guidelines and expert consensus have prescribed and advocated the full examination of the entire stomach [10, 11]. However, these recommendations are not well implemented in clinical practice because of insufficient practical quality control tools and strong supervision [12]. Li et al. reported that completeness of stomach screening was positively related to the detection rate of early cancers. Therefore, it is vital to ensure the completeness of the examinations [13].

With the rapid progress in artificial intelligence (AI) technology, several researchers have developed intelligent systems aimed at diagnosing EGC or upper gastrointestinal neoplasms, and few studies have aimed to ensure the completeness of examinations [14, 15]. In 2019, we first applied deep learning algorithms to the field of endoscopy quality control. We developed WISENSE (renamed ENDOANGEL), an intelligent system aimed at monitoring blind spots in upper gastrointestinal endoscopy in real time [16]. Single-centre and multi-centre randomised controlled trials (RCTs) have proven to significantly reduce the blind spot rate in examinations. Furthermore, we developed ENDOANGEL-LD (lesion detection) to detect gastric abnormalities and diagnose gastric neoplasms (low-grade dysplasia, gastric adenomas, gastric lymphomas, EGC, and advanced gastric cancers) in real time [17]. In another single-centre, tandem-designed trial, we proved that ENDOANGEL-LD could reduce the biopsy rate and miss rates of gastric neoplasms in real time [18].

Development of a tool with the ability to simultaneously improve the diagnostic performance of WLE and ensure high completeness of examination is an ideal way to fulfil these needs. Therefore, we proposed the AI system ENDOANGEL-GC (gastric cancer), which simultaneously combines the functions of blind spot monitoring and lesion detection and runs in real time. We designed this randomised, controlled, patient-blinded, multi-centre trial with two parallel groups and a 1:1 allocation to evaluate the hypothesis that ENDOANGEL-GC would improve the detection rates of gastric neoplasms and EGC.

## Methods/design

### Study design

This is a prospective, single-blind, parallel-group, multicentre, RCT. The recruited participants will be randomised into either the experimental or control groups at a ratio of 1:1. Participants in the experimental group will undergo endoscopic examinations with the assistance of ENDOANGEL-GC, while those in the control group will undergo routine examinations without ENDOANGEL-GC feedback. The study design is illustrated in Fig. 1. This study will be performed according to the Standard Protocol Items: Recommendations for Interventional Trials (SPIRIT) [19]. The SPIRIT Checklist is provided in the supplementary materials. Figure 2 shows the SPIRIT schedule for enrolment, intervention, and assessment.

**Fig. 1 Fig1:**
[figure not shown]
Study design of this trial

**Fig. 2 Fig2:**
[figure not shown]
The SPIRIT schedule of enrolment, interventions, and assessments

### Study setting

This study is being conducted in large-scale, primary hospitals in China.

### Participants and recruitment

Participants who fulfil the following criteria are eligible:

Inclusion criteriaAged ≥ 18 yearsAim to undergo screening, surveillance, and diagnosisUndergo sedated EGDAble to read, understand, and sign informed consent

Exclusion criteriaEGD contraindicationsNot suitable for sedated endoscopy after anaesthesia evaluationBiopsy contraindicationsActive upper gastrointestinal bleeding or emergency oesophagogastroduodenoscopy (EGD)PregnancyUpper gastrointestinal surgery or residual stomachNot suitable for recruitment after investigator evaluation because of other high-risk conditions

## Interventions

### Procedures

The ENDOANGEL-GC is an AI system designed for assisting in EGD and possesses three functions in real time: (1) to time the entire procedure (from the endoscope intubating into the mouth to it being drawn out), (2) to record observed upper gastrointestinal tract landmarks and blind spots, and (3) to mark the upper gastrointestinal lesion with a blue rectangular box (box colour turns red if the lesion is predicted to have a high risk of gastric neoplasm) [16, 17].

The ENDOANGEL-GC is connected to the endoscopy processor, receives digital images as input, and outputs the predictions of landmark monitoring and lesions. The ENDOANGEL-GC is installed on a separate computer system, and the output of the system appears on the same monitor as that of the endoscope. A button on the system is set to switch between “assistance” and “no assistance” modes. Before examination in the control group, the ENDOANGEL-GC is shifted to the “no assistance” mode, so the predictions will be concealed, as they are not displayed on the monitor. Before the examination in the experimental group, the ENDOANGEL-GC is shifted to the “assistance” mode, so the predictions and prompts are displayed on the screen.

The endoscopists who participate in the study are required to have EGD experience with more than 500 cases. All participating endoscopists will be trained in the AI’s functions, including monitoring anatomical landmarks, detecting suspicious lesions, and becoming familiar with the operation requirements during endoscopy. Each endoscopist will perform at least 10 examinations with AI assistance. In both groups, endoscopists are required to screen the entire stomach under white light mode. Only when the screening process is completed and suspicious lesions are found, the image-enhanced mode will be allowed for further judgement. In the experimental group, the endoscopists will operate the endoscope with the assistance of ENDOANGEL-GC. They are required to adhere to the following criteria: (1) screen anatomical landmarks according to the feedback of ENDOANGEL-GC and (2) lesions marked in red boxes by ENDOANGEL-GC are required to undergo biopsy sampling. Lesions that are not marked in red boxes but meet any of the following criteria are also recommended for biopsy: differences in colour, loss of vascularity, slight elevation or depression, nodularity, thickening, abnormal convergence or flattening of folds, irregular margins, irregular discoloration, or irregular surfaces. In the control group, endoscopists will routinely operate on the endoscope. Lesions that meet the above criteria are also recommended for biopsy.

### Adherence and protocol deviations

To enhance the validity of the data, face-to-face adherence reminder sessions and a pilot study will be conducted before enrolment at each study site. Additionally, a key method will be followed for assessing adherence. All raw videos of the examinations, with and without the ENDOANGEL-GC dashboard, will be recorded, stored, and reviewed.

The following conditions will be defined as protocol deviations in the experimental group and will be excluded from the per-protocol (PP) population: (1) more than two anatomical landmarks not observed after video review and (2) biopsy sampling or further treatment not performed for red-box lesions with no pathology results for such lesions.

The following conditions were defined as protocol deviations in both the experimental and control groups and were excluded from the PP population: (1) the inclusion and exclusion criteria are determined to be unfulfilled after the participant is randomised; (2) inability to fully observe the gastric anatomical landmarks due to gastric retention, residual stomach, or oesophageal obstruction; and (3) incorrect mode of ENDOANGEL-GC.

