## Outcomes

The primary outcome measures are detection rate of gastric neoplasms and EGC detection rate. The gastric neoplasm detection rate is defined as the ratio of patients with neoplasms to the recruited population. The EGC detection rate is defined as the ratio of patients with EGC to all patients with gastric cancer. EGC includes pathologically proven high-grade intraepithelial neoplasia and gastric cancer restricted to the mucosa and submucosa.

Secondary outcome measures include the detection rate of premalignant gastric lesions, biopsy rate, observation time, and number of blind spots on EGD examination. The detection rate of premalignant gastric lesions was defined as the ratio of patients with premalignant gastric lesions to the entire recruited population. The biopsy rate is defined as the ratio of patients who undergo biopsy in the recruited population. The observation time is defined as the overall examination time under WLE minus the biopsy operation time. Blind spots are defined as unobserved landmarks.

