### Data analysis plan

The analysis will use intention-to-treat (ITT) and PP approaches. The ITT population will include all patients who are randomised, whereas the PP population will include patients who undergo EGD in accordance with the assigned intervention. The null hypothesis is that the detection rates of gastric neoplasms and EGC in the experimental group will not differ from those in the control group. An alternative hypothesis is that the detection rates of gastric neoplasms and EGC in the experimental group will differ from those in the control group. The experimental group (with ENDOANGEL-GC assistance) will be compared with the control group (without ENDOANGEL-GC assistance) for the two primary outcomes using the *χ*^2^ test.

Continuous variables will be expressed as means (standard deviations [SDs]) or medians (interquartile ranges [IQRs]), according to their distributions, and categorical variables will be presented as numbers (percentages). Baseline characteristics between the two groups will be compared using the *χ*^2^ test for categorical variables and the Mann-Whitney *U* test for continuous variables. Statistical significance is set at *p* < 0.05. A 95% confidence interval will be calculated. Subgroup analysis will be conducted, stratified by multiple indices, such as age and ENDOANGEL-GC-marked red boxes, indicating that only red-box-marked lesions will be included in the analysis. The histological data and lesion characteristics will be compared with the ENDOANGEL-GC prediction, and the performance of ENDOANGEL-GC will be further analysed.

In this study, the potential missing data include the following: (1) characteristic information (the missed data will be marked with “NA” and will not be included in the analysis); (2) pathological results, the gold standards for analysis (participants with missing pathological results are excluded from the analysis); and (3) original videos (the data contained information on whether the endoscopic procedure adhered to the protocol requirements). Participants without this information will be excluded from the per-protocol analyses.

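### Two per-protocol exclusions apply to the AI arm only: this biases any per-protocol blind-spot comparison towards AI by construction, and the neoplasm rate when excluded patients have a below-average yield

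*Protocol article*

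**What the plan says.** Under Adherence and protocol deviations, the protocol article opens its first list with "The following conditions will be defined as protocol deviations in the experimental group and will be excluded from the per-protocol (PP) population". The two items are "more than two anatomical landmarks not observed after video review" and "biopsy sampling or further treatment not performed for red-box lesions with no pathology results for such lesions".

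A second list applies to both arms. Its only item about incomplete observation is "inability to fully observe the gastric anatomical landmarks due to gastric retention, residual stomach, or oesophageal obstruction".

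The Procedures section sets a common duty: "In both groups, endoscopists are required to screen the entire stomach under white light mode". The same section adds, for the experimental group only, that endoscopists follow the landmark feedback and biopsy red-box lesions.

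Under Outcomes, the number of blind spots is a secondary outcome and "Blind spots are defined as unobserved landmarks". For the first primary outcome, "The gastric neoplasm detection rate is defined as the ratio of patients with neoplasms to the recruited population". The second primary outcome, the EGC rate, divides patients with EGC by all patients with gastric cancer.

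The Data analysis plan says "The analysis will use intention-to-treat (ITT) and PP approaches". It also leaves participants with missing pathology out of the analysis, without limiting this to the PP set.

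**The concern.** Both AI-only exclusions depend on what happened after randomisation. A control examination that misses three or more landmarks for a reason such as haste or technique remains in the PP set; an identical AI-arm examination is removed.

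The landmark rule selects on an outcome. It uses the quantity that the blind-spot outcome counts, and it removes from one arm the examinations in which the intervention failed to secure completeness.

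The red-box rule can act on the neoplasm rate. A patient whose only suspicious lesion was never sampled cannot count as a detection. In the full randomised set that patient stays in the denominator; in the PP set the patient leaves it, in the AI arm only. The landmark rule can push the same way, because the article's Introduction cites evidence that more complete stomach screening goes with more early cancers found.

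At stake is whether the PP results can be read as support for the ITT results. As defined, they could show a benefit when there is none.

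**Working it through.** **The plan's own figures.** The PP rule carries no figure. The trial size reproduces: 270 / 0.01 / 0.9 = 30,000, so 15,000 per arm, and 15,000 × 0.9 = 13,500 per arm after the 10% dropout. The control neoplasm rate is 2.5% (Sample size calculation). The documents do not give the share of the AI arm that the two rules would remove, so it is varied below. Every calculation assumes no AI effect.

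**Blind spots.** Assume the same Poisson distribution, mean λ, in both arms. The AI arm is then limited to 0, 1 or 2:

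AI PP mean = [P(1) + 2·P(2)] / [P(0) + P(1) + P(2)]

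For λ = 2: (0.2707 + 2 × 0.2707) / (0.1353 + 0.2707 + 0.2707) = 0.8120 / 0.6767 = 1.20.

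| λ in both arms | AI arm excluded | AI PP mean | Control PP mean | False gain |
|---|---|---|---|---|
| 1 | 8% | 0.80 | 1 | 0.20 |
| 2 | 32% | 1.20 | 2 | 0.80 |
| 3 | 58% | 1.41 | 3 | 1.59 |

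Even the smallest gap would be highly significant. Taking a variance of 1 in each arm, which is conservative for the truncated arm, the standard error at λ = 1 is √(1/13,500 + 1/12,420) = 0.0124, and 0.20 / 0.0124 is about 16.

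**Gastric neoplasm rate.** Let p = 2.5%, f = share of the AI arm excluded, and r = detected-neoplasm rate among those excluded.

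AI PP rate = (p − f·r) / (1 − f), so the gap from control is f·(p − r) / (1 − f).

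The gap favours AI when r < p, is zero when r = p, and reverses when r > p. False-positive risk comes from a two-sided 5% pooled z test with 13,500 × (1 − f) against 13,500.

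Example, f = 10% and r = 0:
- AI PP rate = 2.5 / 0.9 = 2.78% on 12,150 patients; the gap is 0.278 points.
- Pooled rate = (337.5 + 337.5) / 25,650 = 2.63%; standard error 0.200 points.
- z = 0.278 / 0.200 = 1.39, so the chance of rejection is 28%.

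| f | AI PP rate, r = 0 | False-positive risk | AI PP rate, r = 1.25% | False-positive risk |
|---|---|---|---|---|
| 2% | 2.55% | 5.8% | 2.53% | 5.2% |
| 5% | 2.63% | 10.4% | 2.57% | 6.3% |
| 10% | 2.78% | 28% | 2.64% | 11% |
| 20% | 3.13% | 84% | 2.81% | 33% |

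The premalignant-lesion rate is also taken over the recruited population, so the same formula applies.

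**EGC rate.** At 1% gastric cancer, 13,500 patients yield 135 cancers, and 20% of these is 27 EGC. Removing patients without diagnosed cancer leaves 27/135 = 20.0%. Removing 10 advanced cancers gives 27/125 = 21.6%. Removing 5 EGC gives 22/130 = 16.9%. The direction is not fixed.

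**The case against.** **Arm-specific rules have a rationale.** The PP set is meant to hold examinations done as assigned, and following prompts and sampling red-box lesions are AI-arm duties. This stands for the red-box rule as a description of adherence. It is weaker for landmarks, because whole-stomach screening is required in both groups.

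**Some incompleteness is excluded from both arms.** Retention, residual stomach and obstruction are handled symmetrically. A reader might infer that every incomplete control examination stays in; that is not so. The asymmetry concerns the remaining causes.

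**The neoplasm bias is conditional.** It needs r < p. The red-box rule works by lesion, so a patient with another, biopsied neoplasm would leave the numerator too. The general exclusion for missing pathology may already remove some of the same patients, in which case that part of the effect does not come from the PP rule. All of this stands.

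**The size is unknown.** Site training, a pilot at each site and the earlier blind-spot trials that the article mentions all point to a small AI-arm share. At 2% to 5% excluded, the neoplasm distortion is modest. A large blind-spot gap needs a large exclusion: a mean of 4 gives 4 against 1.54, but only with 76% of the AI arm removed.

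**PP does not stand alone.** ITT of all randomised patients is planned, and the neoplasm rate is defined over the recruited population. A reader might infer from the unranked mention of ITT and PP that PP could carry the claim. The article does not say so, and the ranking may sit in an analysis plan that is not shown. Nor does it say specifically that blind spots will be compared in the PP set; this follows only from the general sentence.

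None of these points makes the one-sided landmark rule neutral for a PP blind-spot comparison.

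**Conclusion.** The defect is real and confined to the PP definition.

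- **Blind spots:** a PP comparison is biased towards AI by construction whenever any AI-arm examination is removed by the landmark rule. The false gain is 0.2 to 1.6 landmarks for assumed Poisson means of 1 to 3.
- **Gastric neoplasm and premalignant-lesion rates:** the bias favours AI if excluded patients have a below-average yield. For the neoplasm rate, false-positive risk runs from about 5% to 84% across assumed exclusion shares of 2% to 20% and yields of half or none.
- **EGC rate:** the heavier reading, that both primary outcomes are mechanically favoured, is not supported. This rate counts only diagnosed cancers in its denominator and can move either way.

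The landmark exclusion leaves the ITT set untouched. With ITT planned and the exclusion share unknown, this is a should-fix point and does not threaten the trial's main comparison.

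**What to change.** - **Landmark rule:** drop the AI-only exclusion from the PP definition. If it is kept, apply it to both arms from the same video review and state that it conditions on an outcome the intervention is meant to change. Applying it to both arms is second best, because it also deletes control misses that are part of the effect under test.
- **Red-box rule:** drop it from the PP detection analysis and report the share of red-box lesions without pathology as an AI-arm adherence rate.
- **Blind spots:** do not analyse them in a PP set selected on landmarks.
- **Conclusion:** rest it on ITT, with PP labelled supportive.

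The cost is wording, since videos of all examinations are already to be recorded and reviewed. The downside is a PP set that reflects adherence to AI prompts less strictly, or a smaller control PP set if the landmark rule is applied to both arms. Enrolment was under way when the article was submitted, so the change should be dated and made before any results by arm are seen.

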## Recruited cases

### Consent

Patients eligible to participate in this study will be provided with further discussions and informed consent. Discussions may be completed by a local study coordinator or a staff member. Written informed consent will be obtained from all participants who agree and wish to take part in the study.

